## Abstract

**Background:**

Research indicates that university students experience higher levels of stress, anxiety, and depression (SAD) than the general population. In Uganda, existing psychological interventions for addressing SAD among students are primarily delivered face to face, which limits effective diagnosis and treatment due to stigma, a shortage of counselors, and long waiting times, which contribute to significant unmet mental health needs. Consequently, there is an urgent need for innovative approaches to improve access to mental health services.

**Objective:**

This study aims to assess the feasibility and effectiveness of a supportive SMS text messaging program (Wellness4Students [W4S]) in reducing the prevalence of SAD among university students in Uganda.

**Methods:**

This study has a quantitative longitudinal research design. We will target 4494 undergraduate students aged 18 to 24 years who will be recruited from Makerere University, Uganda. Through advertisements on social media platforms (WhatsApp and X [formerly known as Twitter]) and websites, students will receive a link to the W4S website with information about the intervention. Eligible students will voluntarily self-subscribe to the W4S program by providing their email addresses. The subscription will be an indicator of consent required for participation in receiving the intervention. Subscribers will receive daily supportive messages for 6 months. The data will be collected from subscribers at baseline (program initiation), 1 month, 3 months (midpoint), and 6 months (program completion) through web-based surveys. Students will complete questionnaires regarding SAD and well-being. We will conduct both descriptive and inferential statistical analyses using STATA version 17.

**Results:**

The results of this study are expected within 1 year after program initiation. The data will be collected from February 2026 through October 2026. The development of the W4S app and the survey instrument has been completed. The cocreation of mental health messages with 15 undergraduate students and 2 university psychologists has been completed as of March 23, 2026. The roll-out of the program is scheduled for March 24, 2026.

**Conclusions:**

The W4S intervention is feasible. The W4S program will provide essential insight into the prevalence and correlates of SAD among Makerere University students. We will identify students who are most at risk of poor mental health outcomes.

## Introduction

### Background

Mental health is a critical component of overall well-being. Mental health disorders, such as stress, anxiety, and depression (SAD), have been linked to serious health conditions [1], including cardiovascular diseases, cancer, diabetes, respiratory diseases, substance abuse, chronic pain, sleep disorders, and heart diseases [2]. Globally, mental health disorders are among the most burdensome health problems, accounting for more than 970 million cases [3,4]. According to the United Nations Children’s Fund, more than 13% of young people are affected worldwide [5]. Anxiety and depression alone comprise about 40% of these cases [5]. While these statistics reflect a worldwide crisis, the burden is disproportionately higher in low- and middle-income countries, where mental health infrastructure is underresourced and access to care is critically limited [2,6,7].

In sub-Saharan Africa, this disparity is glaring. The continent has fewer than 1.5 mental health workers per 100,000 population, compared to a global median of 9, and governments allocate less than 1% of health budgets to mental health [2,4,8]. This scarcity is linked to the treatment gap, estimated at over 75% for common mental disorders in sub-Saharan Africa, leaving the vast majority without any form of care [9]. This systemic neglect exacerbates vulnerabilities among populations already facing socioeconomic challenges, including university students.

Evidence consistently indicates a higher prevalence of SAD among university students compared to the general population [10-12]. Multiple meta-analyses indicate that university or postsecondary students have far higher pooled rates of depression and anxiety than the general or same-age population. For instance, a large pre-COVID meta-analysis estimated depression prevalence among university students at 30.6%, far above the global adult prevalence of 12.9% [13]. A more recent global review (64 studies; 100,187 students) found a pooled prevalence of depression at 33.6% and anxiety at 39% among college students [14]. An umbrella review of anxiety in college or university students across all world regions reported a median anxiety prevalence of 32% (range 7.4%‐55%) [15]. A systematic review covering 40 countries found a prevalence of 26.1% for depression and 24.5% for anxiety among university students and explicitly contrasted this with much lower World Health Organization estimates for the general population (depression: 4.4%, anxiety: 3.6%), concluding that disorders “affect a much higher percentage of university population than the general one.” The transition into higher education presents a key developmental period marked by academic pressure, social reorientation, and often financial strain, all of which can significantly impact mental health [16]. These problems not only cause personal distress but also negatively affect students’ quality of life and academic performance [17].

Research across East Africa highlights the scale of the issue, though prevalence estimates vary due to methodological heterogeneity in assessment tools and timing. In Tanzania, a study reported a prevalence of depression of 22% among undergraduates [17], while in Kenya, the prevalence reached 41% [18]. In Uganda, a systematic review found that depression among university students ranged from 0.4% to 80% [16], a range underscoring the need for standardized measurements. A study among medical students at Makerere University found a prevalence of 22% [19]. The COVID-19 pandemic remarkably exacerbated this situation; during the lockdowns, one study among Ugandan students reported alarmingly high rates of depression (81%), anxiety (98%), and stress (78%) [20]. This dramatic increase aligns with global findings of a “mental health pandemic” secondary to COVID-19, particularly affecting youth in educational settings [16].

Digital mental health interventions, delivered through widely accessible platforms like email and WhatsApp, offer a promising pathway. Systematic reviews suggest that digital interventions, particularly those based on cognitive behavioral therapy (CBT) principles delivered via text or app, are effective in reducing symptoms of depression and anxiety in young adults [39,40]. They can provide stigma-free and consistent support, directly addressing gaps in accessibility and human resources. Their scalability makes them particularly suitable for low-resource settings. Preliminary studies in other African contexts, such as SMS-based support for perinatal depression in Kenya, demonstrate feasibility and high acceptability [41,42]. This study responds to this urgent need by assessing the feasibility and effectiveness of a supportive SMS text messaging program (Wellness4Students [W4S]) in reducing the prevalence of SAD among university students in Uganda.

### W4S Email and WhatsApp Messaging Intervention

The W4S program is a daily, supportive email and WhatsApp messaging intervention designed to mitigate symptoms of SAD and promote well-being. It is part of the broader ResilienceNHope suite, supported by a web-based platform and implemented through the Global Psychological eHealth Foundation. The initial content is developed by mental health professionals using CBT principles. Crucially, for this study, the program will be contextually adapted. The initial message database contains generic content that will serve only as a starting point for adaptation. Through participatory cocreation workshops with students at Makerere University, this content will be linguistically, culturally, and contextually adapted to ensure that metaphors, proverbs, and messages address specific contextual stressors for the students. This participatory process is central to the intervention’s design, ensuring it is not merely imported but is collaboratively shaped by its intended users [25,28,33,43].

Through a partnership with Makerere University, students will be able to self-enroll online. Upon registration, they will receive daily supportive, noninteractive (one-way) messages for 6 months, with the nature of the service clearly explained at the outset. Each day’s email and WhatsApp message will be unique, drawn from a large message database.

Examples of messages (not yet adapted) to be delivered to subscribers of the W4S email and WhatsApp messaging program include the following:

What you do today will determine how you are tomorrow. Rise up and take advantage of whatever opportunities today presents, and success will be yours tomorrow.There are 2 days in the week we should not worry about, yesterday and tomorrow. That leaves today, live for today.There are no surprises in store. You are in charge of the successes that await you. There may be some challenges, but you have the power to overcome them.

### Aims of the Study

This study aims to determine the prevalence and correlates of SAD among university students in Uganda. It also aims to determine if daily supportive text messages can help reduce the prevalence of SAD and improve well-being among university students.

### Specific Objectives

This study has the following objectives: (1) to determine the prevalence and correlates of SAD among university students in Uganda, (2) to investigate the effectiveness of the daily W4S supportive messages in reducing levels of SAD and in improving well-being among university students in Uganda, and (3) to investigate the participants’ experience and satisfaction associated with the W4S daily SMS text messaging support.

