## Methods

### Study Design

The study used a quantitative longitudinal study design. It will be implemented in three phases: (1) the cocreation and adaptation of the intervention; (2) the baseline survey; and (3) follow-up surveys conducted at 1 month, mid-term follow-up at 3 months, and an endline at 6 months. The cocreation phase was completed during the recess term (July 2025). The next 2 phases, baseline and follow-ups, will be implemented between February 2026 and October 2026. Recruitment will begin in February 2026 and will last for 3 months up to April 2026. There will be an observation period of 6 months for the enrolled participants [28,33,43].

The email and WhatsApp messaging intervention was cocreated and adapted by the study team together with purposively selected students and identified stakeholders. Thereafter, a baseline survey will be conducted before recruitment to estimate the prevalence of SAD. Students at Makerere University will be invited via email and WhatsApp to self-subscribe to the W4S program. All participants who subscribe to the intervention will receive a link to the online baseline survey, daily supportive messages for 6 months, and the follow-up survey links at 1-, 3-, and 6-month postenrollment time points [33,43].

The rationale for the nonrandomized design is based on resource constraints. We have funding to implement a pilot survey and use the preliminary results to apply for a bigger grant to implement a fully randomized controlled trial.

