There are several adaptation frameworks. These include the ADAPT-ITT (Assessment, Decision, Adaptation, Production, Topical experts, Integration, Training, Testing), intervention mapping (IM) framework, and framework for reporting adaptations and modifications to evidence (FRAME), among others [38,45,46]. For this study, we will adapt the W4S program [33,43] using the IM adaptation framework [47]. The IM adaptation framework has 6 steps. First, establish a detailed understanding of the health problem, the population at risk, the behavioral and environmental causes, and the determinants of these behavioral and environmental conditions and assess available resources. Second, describe the behavioral and environmental outcomes, create objectives for changes in the determinants of behavior and environmental causes, and specify the targets of the intervention program. Third, identify theory- and evidence-based behavior change methods that influence the determinants and translate these to practical applications that fit the intervention context. Fourth, combine the intervention components into a coherent program that uses delivery channels that fit the context. Fifth, develop implementation strategies to facilitate the adoption, implementation, and maintenance of the program. Finally, plan both process and outcome evaluation to assess program implementation, efficacy, or effectiveness [47].

The adaptation is expected to improve the feasibility and acceptability of the W4S intervention [33-35,43]. The cocreation and adaptation will be done when students are in the recess term period (between June and July).

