### Hypotheses

We hypothesize that the W4S email and WhatsApp messaging program will reduce the prevalence and severity of SAD among Makerere University students. We also hypothesize that the prevalence of moderate-to-high stress, moderate-to-high anxiety, and moderate-to-high depression would be comparable to the prevalence of these conditions reported among university students in East Africa (Kenya and Tanzania) and in other jurisdictions. Finally, we hypothesize that demographic factors, socioeconomic factors, organizational factors, and class size will be associated with SAD among students.

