## Results

The results will be reported following the SPIRIT (Standard Protocol Items: Recommendations for Interventional Trials) checklist [63]. The W4S email and WhatsApp messaging program was anticipated to be launched in September 2025. There were some delays, and the enrollment will start by March 24, 2026. Enrollment is expected to continue for 6 months up to September 2026. Data collection will continue for another 6 months. The results of the study will be disseminated to stakeholders in the education sector in Uganda, East African countries, and globally through workshops, conference presentations, and peer-reviewed publications.

The progress to date is that ethical approval has been secured. We conducted a cocreation of intervention messages. A pilot survey was conducted with about 20 students. We are going to implement the enrollment and the intervention during the second semester of the academic calendar (February-May 2026). We will implement a survey from March 2026 at different time intervals.

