## Discussion

### Principal Findings

SAD may indirectly hinder university students’ academic performance, overall lifestyle, psychological safety, and well-being, as well as lead to other physical health problems. Given their demanding schedules, students need innovative, anonymized, accessible, convenient, and cost-effective programs to support their mental health. This protocol proposes the use of supportive email and WhatsApp messages as a psychological intervention for students experiencing SAD. Those with any of the target outcomes, prior traumatic experiences, or adverse childhood events are expected to benefit particularly from this program. We anticipate a reduction in mental health outcomes, such as reduced SAD among university students at Makerere University.

The study will generate important information on the prevalence and correlates of SAD among students at Makerere University, Kampala, Uganda. It will also provide valuable insights into the application of eHealth approaches for young populations within the education sector. The effectiveness of daily supportive email and WhatsApp messaging in addressing these mental health concerns will be evaluated, offering critical evidence to guide school policies and decisions on psychological interventions for students in low- and middle-income countries.

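### The protocol sets out to test effectiveness, but one fully treated group compared with its own baseline can only show change among subscribers

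*Protocol article*

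**What the plan says.** **The claim.** Specific Objectives gives Objective 2 as "to investigate the effectiveness of the daily W4S supportive messages in reducing levels of SAD". The Abstract objective and Aims of the Study say much the same. Hypotheses states: "We hypothesize that the W4S email and WhatsApp messaging program will reduce the prevalence and severity of SAD among Makerere University students". Principal Findings says: "The effectiveness of daily supportive email and WhatsApp messaging in addressing these mental health concerns will be evaluated", and adds that the evidence is meant to guide school policy.

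**The design.** Study Design says: "All participants who subscribe to the intervention will receive a link to the online baseline survey, daily supportive messages for 6 months". There is no untreated, delayed or other concurrent group. It explains: "The rationale for the nonrandomized design is based on resource constraints", and describes the study as a pilot towards a randomised trial. Conclusions calls the evidence preliminary.

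**The analysis.** Statistical Analysis compares mean scores and prevalence at baseline, 1, 3 and 6 months by paired t tests and proportion tests. Background characteristics are controlled only in profile plots.

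**Other exposures.** Data Collection lets participants see their scores and receive recommendations according to severity. Ethical Considerations provides referral for those with adverse outcomes.

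**Limitations.** Strengths and Limitations covers unknown duration of effect, non-diagnostic scales, generalisability and low response. It does not mention the absent comparator, regression to the mean or the calendar.

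**Dates.** Results says enrolment starts by 24 March 2026 and: "We are going to implement the enrollment and the intervention during the second semester of the academic calendar", dated February to May 2026. Study Design closes recruitment in April; Results also says enrolment runs to September. The recess is dated in the intervention section (adaptation is to be done "when students are in the recess term period (between June and July").

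**The concern.** The objective asks a causal question, while the design and test answer a descriptive one. A paired test asks whether the mean moved. It does not ask why, and here several things change together with the messages:

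- **Time.** Scores may drift for reasons unrelated to the programme.
- **Selection.** Volunteers for a mental health programme may enter with scores above the student average, and such scores tend to fall on re-measurement.
- **Academic calendar.** The Background names academic pressure as a cause of SAD, and follow-up may fall in a different academic period from baseline.
- **Score feedback and referral.** Both could change outcomes, and any benefit would be credited to the messages.

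No later analysis plan can supply a comparator that the design lacks, so this is not a detail the article has left to another document. At stake is a significant fall being reported as evidence that the messages work, in a study intended to inform policy and support a larger grant application.

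**Working it through.** **1. The plan's own figures** (Sample Size Estimation)

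- Prevalence: 1.96² × 0.25 / 0.02² = 2400.9. With the finite-population correction for 35,000 this is 2246.8, so 2247. Then 2247 / 0.5 = 4494. Both are reproduced.
- Before-after test: reading the 30% effect as a standardised paired difference of 0.30, the normal approximation gives (1.960 + 0.842)² / 0.30² = 87.2. The exact noncentral t gives n = 90 (power 0.804; n = 89 gives 0.799). This is also reproduced.

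The arithmetic is sound. The issue is what a significant result could mean.

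**2. The test's response to drift that is not a message effect**

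The same power function applies whatever causes the shift. In units of the SD of the paired change, with zero message effect:

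| Drift | n = 90 | n = 449 | n = 2247 |
|---|---|---|---|
| 0.10 | 16% | 56% | 99.7% |
| 0.20 | 47% | 99% | about 100% |
| 0.30 | 80% | about 100% | about 100% |

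At n = 90, a drift of 0.30 from any source is declared significant as often as the planned effect. At 2247 pairs, a drift of 0.059 is enough for 80%. The 449 is about 20% of 2247, shown for scale. The protocol's 2247 is baseline completers, so using it as pairs assumes no attrition.

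**3. Regression to the mean, for scale**

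These inputs are assumptions, not in the documents: subscribers' baseline mean is k = 0.1 to 0.5 SD above the population mean; test-retest correlation r is 0.5 to 0.8; the SD is the same at both times.

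- Expected fall = k(1 − r). SD of change = √(2(1 − r)). Paired effect d = k(1 − r) / √(2(1 − r)).
- Lowest: k = 0.1, r = 0.8. Fall = 0.1 × 0.2 = 0.02 SD; d = 0.02 / √0.4 = 0.032.
- Highest: k = 0.5, r = 0.5. Fall = 0.5 × 0.5 = 0.25 SD; d = 0.25 / √1 = 0.25.

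| | n = 90 | n = 449 | n = 2247 |
|---|---|---|---|
| Lowest | 6% | 10% | 32% |
| Highest | 65% | about 100% | about 100% |

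The nominal rate is 5%.

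**4. Calendar**

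| Enrolled | Month 1 | Month 3 | Month 6 |
|---|---|---|---|
| 24 March 2026 | 24 April | 24 June | 24 September |
| 30 April 2026 | 30 May | 30 July | 30 October |
| 30 September 2026 | 30 October | 30 December | 30 March 2027 |

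If enrolment closes in April, every baseline is in the February to May semester and every month-3 survey is in June or July, the stated recess. Month 1 stays within the semester dates. If enrolment runs to September, baseline and follow-up fall at mixed points of the year. The April closure fits the Abstract's data collection to October 2026; the September closure does not.

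**The case against.** **The protocol already hedges.** It states that the study is nonrandomized, gives the reason, calls it a pilot and describes the evidence as preliminary. This is true and counts in its favour. But the hedge does not reach the objective, the hypothesis or the limitations, and a reason for not randomising does not license an effectiveness claim.

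**Recess at month 3 is not certain.** This stands. A reader might infer that the month-3 contrast is semester against recess for everyone; that holds only with April closure. The June-July dates are given for the cocreation work, which Study Design places in July 2025, and are carried over to 2026. Nor do the documents say that stress is lower in the recess term. What survives is that calendar time and time on the programme are not separated by the paired tests under either window.

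**Regression to the mean is not documented.** This also stands. A reader might infer that students sign up because they feel bad, so that a programme with no effect would be declared effective. The documents do not say so: there is no entry threshold, students with or without SAD may enrol, recruitment is by broadcast, and participants are compensated. It is plausible, of unknown size, and the low end of the range at n = 90 barely exceeds 5%.

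**Analysis cannot readily repair it.** Correct. With April closure, academic period coincides with visit for the baseline to month-3 contrast and cannot be adjusted for. Early entrants' follow-up then overlaps later entrants' baseline only on about 24 to 30 April, at month 1. Non-subscribing baseline completers exist only if the baseline survey precedes subscription, as in Data Collection; Study Design and the recruitment section put subscription first. That is why the remedy rests on the stated claim.

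**Conclusion.** The point holds as a mismatch between claim and design. Effectiveness is the stated objective, every subscriber is treated, the only test is against own baseline, and the missing comparator is not listed as a limitation. This rests on the text alone and needs no numerical assumption.

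The size of any false signal is unknown. The ranges in the working (6% to 65% at n = 90; 32% to about 100% at 2247 pairs) depend on an assumed starting shift and retest correlation, and the upper sample size assumes no loss to follow-up. They show that the paired test can reject often without a message effect, not that it will. The semester-to-recess contrast at month 3 is conditional on April closure; confounding with calendar time is not. The sample size arithmetic is correct and is not in question.

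**What to change.** 1. Reword Objective 2, the aims (Abstract and Aims of the Study), the hypothesis, Principal Findings and Conclusions to describe change in SAD over 6 months among subscribers. Reserve effectiveness for the planned randomised trial.
2. In Strengths and Limitations, name the absent comparator, regression to the mean, the academic calendar, and score feedback with referral as limits on causal interpretation.
3. Reconcile the enrolment window between Study Design (to April 2026) and Results (to September 2026), together with the data collection period.
4. Only if enrolment will span several academic periods, consider adjusting for academic period at each survey date and comparing early entrants' follow-up with later entrants' baseline in the same calendar month.
5. Optionally, follow up baseline completers who do not subscribe, as a descriptive comparison. This is possible only if baseline precedes subscription. The group would be non-random, and it would need consent wording and possibly further participant compensation.

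Items 1 to 3 are text changes. Their cost is a less favourable stated claim.
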